## Abstract

**Background:**

On the national level, nutritional monitoring requires the assessment of reliable representative dietary intake data. To achieve this, standardized tools need to be developed, validated, and kept up-to-date with recent developments in food products and the nutritional behavior of the population. Recently, the human intestinal microbiome has been identified as an essential mediator between nutrition and host health. Despite growing interest in this connection, only a few associations between the microbiome, nutrition, and health have been clearly established. Available studies paint an inconsistent picture, partly due to a lack of standardization.

**Objective:**

First, we aim to verify if food consumption, as well as energy and nutrient intake of the German population, can be recorded validly by means of the dietary recall software GloboDiet, which will be applied in the German National Nutrition Monitoring. Second, we aim to obtain high-quality data using standard methods on the microbiome, combined with dietary intake data and additional fecal sample material, and to also assess the functional activity of the microbiome by measuring microbial metabolites.

**Methods:**

Healthy female and male participants aged between 18 and 79 years were recruited. Anthropometric measurements included body height and weight, BMI, and bioelectrical impedance analysis. For validation of the GloboDiet software, current food consumption was assessed with a 24-hour recall. Nitrogen and potassium concentrations were measured from 24-hour urine collections to enable comparison with the intake of protein and potassium estimated by the GloboDiet software. Physical activity was measured over at least 24 hours using a wearable accelerometer to validate the estimated energy intake. Stool samples were collected in duplicate for a single time point and used for DNA isolation and subsequent amplification and sequencing of the 16S rRNA gene to determine microbiome composition. For the identification of associations between nutrition and the microbiome, the habitual diet was determined using a food frequency questionnaire covering 30 days.

**Results:**

In total, 117 participants met the inclusion criteria. The study population was equally distributed between the sexes and 3 age groups (18-39, 40-59, and 60-79 years). Stool samples accompanying habitual diet data (30-day food frequency questionnaire) are available for 106 participants. Current diet data and 24-hour urine samples for the validation of GloboDiet are available for 109 participants, of which 82 cases also include physical activity data.

**Conclusions:**

We completed the recruitment and sample collection of the ErNst study with a high degree of standardization. Samples and data will be used to validate the GloboDiet software for the German National Nutrition Monitoring and to compare microbiome composition and nutritional patterns.

**Trial Registration:**

German Register of Clinical Studies DRKS00015216; https://drks.de/search/de/trial/DRKS00015216

**International Registered Report Identifier (IRRID):**

DERR1-10.2196/42529

## Introduction

Within the last decade, there has been a huge increase in research in the field of the human microbiome, leading to a new body of knowledge in this area. It is now well established that the human intestinal microbiome is an essential mediator in the interplay between diet and host physiology. Initiatives like the HDHL-INTIMIC Knowledge Platform on Food, Diet, Intestinal Microbiomics, and Human Health [1] were founded to collect and extend this knowledge by fostering multidisciplinary projects.

Many associations between diet and the microbiome have been described, for example, correlations of the long-term diet with differences in gut microbiota composition and functions [2-7]. However, until now, only a small part of gut microbiota variation has been attributed to nutrition [8]. The usual dietary pattern has a strong influence on microbiota composition, as has been shown for plant-rich diets such as the Mediterranean diet, vegetarian or vegan habits, and the abundance of *Prevotella* species [9-12]. It is important to understand how nutrition impacts microbiota, as a disturbance in the latter (dysbiosis) has been associated with many diseases, including diet-related diseases such as obesity and type 2 diabetes. Many studies have been performed on such specific topics, but the results are often inconsistent or even contradictory [13-15]. Such a variety of results can be partially explained by differences in the study population, but also by a lack of standardization of methods, including sample preparation, technology, and bioinformatic analysis [16-18].

Besides the importance of standard methods to determine the microbiome composition, the assessment of reliable representative dietary intake data also requires standardized and validated tools that are up-to-date with recent developments in food products and the nutritional behavior of the population. In Germany, the Max Rubner-Institut (MRI) is responsible for the national nutrition monitoring of the adult population and has so far conducted the second German National Nutrition Survey [19] and the longitudinal study NEMONIT [20]. National nutrition monitoring serves to assess food consumption, nutritional status, and nutritional behavior of the general population and specific population groups. In addition, trends in the nutritional behavior of the population can be monitored. The data are used to update national food-based dietary guidelines, to perform risk assessment by food consumption of the population toward chemical substances in food items, and to serve as decision support for national and European statutory rules. Sound and representative data on nutrition are, therefore, essential for policy-making, answering scientific questions, providing information on the population, and making national and international comparisons.

In this context, the European Food Safety Authority (EFSA) developed methodological guidelines for data assessment in national food consumption surveys [21,22]. Accordingly, 24-hour recalls should be applied to national nutrition monitoring as a dietary assessment method for the adult population. The software GloboDiet (previously EPIC-Soft; International Agency for Research on Cancer), developed as a software platform for a standardized, structured interview, fulfills the EFSA recommendations and thereby provides data with the required detail and quality for national nutrition monitoring [23,24]. In some countries across the European Union, GloboDiet is used for the assessment of representative detailed food consumption data [25,26]. GloboDiet was adapted for the German food market. For example, new foods available on the food market were added and obsolete foods were deleted. In addition, adjustments were made to the description and quantification of the foods in accordance with the abovementioned objectives of the German National Nutrition Monitoring. The standard units to assess the consumed quantity of different food items were updated, and the descriptions of the foods were adjusted to enable analyses of the consumption of ultraprocessed foods.

The ErNst (“Erfassung der Energie- und Nährstoffzufuhr”; English “assessment of energy- and nutrient intake”) study was conceived to address two independent objectives: (1) to verify whether food consumption, as well as energy and nutrient intake of the German population, can be recorded validly by means of the current version of the dietary recall software GloboDiet for the German National Nutrition Monitoring and (2) to obtain biosamples and high-quality data for an exploratory assessment of associations between dietary intake, microbiome composition, and microbial metabolites (as a proxy for functional activity of the microbiome). The purpose of this manuscript is to provide a comprehensive description of the study protocol and the methods used for the collection of biosamples and dietary intake data, combined with an overview of the number of samples and data points that will be available for further analysis.

## Methods

### Study Design and Setting

The ErNst study was designed as a cross-sectional observational study and performed at the Division of Human Studies of the Department of Physiology and Biochemistry of Nutrition at the MRI, Karlsruhe, Germany, between October and December 2018. On day 1, all volunteers visited the study center for registration, further instructions, application of the accelerometer device, and initial measurements (visit 1, Figure 1). Furthermore, participants were informed about the study procedures and gave their written consent (see also Ethics Approval). Either on the first or second day after the initial visit, participants collected stool and 24-hour urine samples at home (collection day) and brought them on the second visit to the study center the day after (visit 2). Questionnaires and interviews on nutritional intake were also completed on this day.

During visits 1 and 2, the participants underwent a series of standardized examinations described in detail below. For all interviews, examinations, measurements, sample collection, sample preparation, and storage, standard operating procedures were developed and tested for feasibility. Interviewers and examiners had been extensively trained and supervised during data collection.

**Figure 1 figure1:**
[figure not shown]
Overview of the ErNst (Erfassung der Energie- und Nährstoffzufuhr) study days. Collection day was either on the first or second day after visit 1. Visit 2 followed immediately the day after collection day. BIA: bioelectrical impedance analysis.

### Participants

Female and male volunteers aged 18-79 years without any known or apparent acute or chronic illnesses or diseases were eligible to participate. Detailed inclusion and exclusion criteria are listed in Textbox 1. Health status questionnaires were used to assess medical history, including potential confounding variables like the use of antibiotics within the last 12 months and smoking status.

Recruitment procedures included direct communication with previous study participants and MRI employees and their families, the use of flyers and other information materials provided to institutions in and around Karlsruhe, information about the study on MRI’s homepage, and word of mouth. Initially, 230 interested persons contacted the study center (Figure 2). Those who passed an initial telephone interview (done with a checklist) were scheduled for their first study visit (n=133). Reasons for the exclusion of interested persons are also given in Figure 2. Participants included in the study were asked to complete a questionnaire regarding their marital status, partner relationship status, household size (the number of people living in the household, including children), net monthly household income, school education (highest school-leaving qualiﬁcation), and occupational qualification.

Since the software GloboDiet shall be validated for the German National Nutrition Monitoring of the adult population, we recruited the participants of the ErNst study according to 3 preselected age groups (18-39, 40-59, and 60-79 years). The proportion of men and women in the respective age groups was equal, as was the total number of participants in each of the 3 groups.

Criteria for inclusion and exclusion.
**Inclusion criteria**
Healthy female or maleAble to complete all planned examinations, interviews, and questionnairesWritten consent to participate voluntarily in the studyAged between 18 and 79 years
**Exclusion criteria**
Pregnant or breastfeedingDiabetes mellitusRenal diseaseUse of diureticsHyper- or hypothyreosisCurrently on diet to reduce weightTechnical implants (such as pacemaker)Amputation of arms or legsDiseases and treatments leading to malabsorption of energy and nutrientsBlood donation within last 4 weeksInsufficient German language to complete interviewsUse of antibiotics within last 12 monthsTumors requiring therapyAcute or chronic infectious diseaseAbuse of drugs or alcoholLikely failure to comply with study conditionsPersons who are kept in an institution by court or official orderFailure or unwillingness to provide written consent of participation

**Figure 2 figure2:**
[figure not shown]
Flowchart describing the recruitment process and available data points of the ErNst (Erfassung der Energie- und Nährstoffzufuhr) study. The bifurcation of the available data separates long-term and short-term (current) data points. FFQ: food frequency questionnaire.

### Anthropometric Measurements and Assessment of Body Composition

Anthropometric data were assessed using standard methods. Participants were asked not to eat or drink for 4-5 hours before the examination.

Body weight was measured to the nearest 0.05 kg in light clothing without shoes, and height was measured to the nearest 0.1 cm using the seca 285 measurement station (seca). Both parameters were used to calculate the respective BMI (kg/m²).

Bioelectrical impedance analysis (BIA) was used to assess body composition with the measurement device Nutriguard-MS (Data Input GmbH) using multifrequency technology (5.50-100 kHz; 0.8 mA). The analysis was conducted with NutriPlus software (version 5.3.0; Data Input GmbH).

### Assessment of Physical Activity and Calculation of Total Energy Expenditure

The activity energy expenditure (AEE) was determined using accelerometers (ActiHeart from CamNtech) for at least 24 hours. Here, the heart rate was recorded together with the acceleration data, so that activities that took place in a sitting position and where the subject itself experienced little acceleration (eg, cycling) could also be adequately depicted. The software used for programming and reading out the acquired data was the ActiHeart software (version 4.0.131; CamNtech).

Resting metabolic rate (RMR) was calculated according to the formula of Müller et al [27] and considered fat-free mass as well as fat mass and the age of the participants.

Dietary-induced thermogenesis (DIT) accounts for about 10% of the energy content of the consumed food [28-30]. Total energy expenditure (TEE) was calculated using the following formula: TEE (kcal) = RMR (kcal) + AEE (kcal) + DIT (kcal)

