### Assessment of Current Food Consumption by Applying the Software GloboDiet (24-Hour Recall) and Calculation of Energy and Nutrient Intake

During the second visit to the study center, the food consumption of the participants was assessed face-to-face by trained interviewers using the software GloboDiet. The software was adapted to the current German food market and modified for use in the German National Nutrition Monitoring of the adult population. The structure and standardization procedures of GloboDiet have been described in detail elsewhere [24]. For the 24-hour recall, participants were asked in detail about their food and beverage consumption, as well as the use of dietary supplements on the previous day. Corresponding to a first so-called quick list of the consumed foods and beverages in chronological order of the meals, the reported food items were further described by facets and descriptors (eg, the applied preparation method, the preservation method, the flavor, and the fat content). Consumed quantities were assessed with a picture book, household measurements, as well as standard units. Interviews were conducted on Mondays, Wednesdays, and Thursdays, leading to results of food consumption on Sundays, Tuesdays, and Wednesdays, representing a balanced coverage of weekdays and weekends, which was intended regarding the validation of the GloboDiet software.

Based on the assessed food consumption, energy and nutrient intake were calculated using data from the German Nutrient Database version 3.02 [31].

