### Analysis of Biomarkers in Urine

#### Overview

The validation of the German GloboDiet version will use an approach with nitrogen and potassium urinary excretion as biochemical markers for protein, as well as potassium intake [36,37]. Nitrogen and potassium excretion were chosen because errors are likely to be independent between the measurements of biomarkers and dietary intake [38,39].

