## Discussion

### Principal Findings

Within the study, 117 participants completed the recruitment. After the subtraction of some errors in sample collection and measurements, 106 stool samples are available with corresponding data on common nutrition (30-day FFQ). In addition, 109 face-to-face 24-hour recalls were conducted (data on current nutrition), with corresponding urine samples and measured urine parameters. For 82 of these data sets, additional data on physical activity have been collected.

The 2 main aims of the study were to collect samples and data for (1) validating the dietary recall software GloboDiet and (2) for studying the association between diet and the intestinal microbiome. The 117 participants who successfully completed the study were equally distributed with respect to sex and age groups. However, the fraction of participants with a BMI above 25 kg/m² was lower in the study (females: 18/61, 29.5%, males: 27/56, 48.2%) than observed in the official representative statistics of the German population in 2017 (females: 43.1%, males: 62.1%, data set 12211-9018 in the Genesis database [44]). In addition, the average level of education is high in the study population. Therefore, the study population could be somewhat biased toward a healthier lifestyle, including nutrition and activity, than would be expected in the general population.

For the validation of the updated GloboDiet version, protein and potassium intake determined with the software will be compared with the excretion of protein and potassium in the 24-hour urine collection. In addition, EI calculated from the 24-hour recall will be compared to TEE and RMR. To estimate the validity of the current GloboDiet version, different methods will be applied, like the Wilcoxon-signed rank test to test if the differences between nutrient excretion and nutrient intake, as well as TEE and EI, are different from zero, Spearman rank correlation coefficients to assess the strength of the correlations, as well as Bland-Altman plots [45,46]. Bland-Altman diagrams are suitable for visualizing measurement differences. In addition, participants will be grouped into tertiles to assess the agreement in ranking participants regarding nutrient intake and excretion, as well as EI and TEE. Furthermore, for EI, cutoff values according to Goldberg et al [47] and Black [48] will be calculated for group levels as well as for individuals.

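### As written, total energy expenditure contains about 10% of the reported intake, so the reference for energy shares recall error with the method it is used to validate

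*Protocol article*

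**What the plan says.** The Methods section on physical activity and TEE gives TEE as the sum of three terms.

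- **AEE** comes from a device: "The activity energy expenditure (AEE) was determined using accelerometers (ActiHeart from CamNtech) for at least 24 hours".
- **RMR** comes from a published formula that "considered fat-free mass as well as fat mass and the age of the participants".
- **DIT** is the only term tied to diet: "Dietary-induced thermogenesis (DIT) accounts for about 10% of the energy content of the consumed food".

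The Methods section on the 24-hour recall describes the one source of same-day energy intake: "Based on the assessed food consumption, energy and nutrient intake were calculated using data from the German Nutrient Database version 3.02". The food frequency questionnaire covers the past four weeks and is also self-reported.

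Principal Findings then says that "EI calculated from the 24-hour recall will be compared to TEE and RMR". The methods listed for EI against TEE are a Wilcoxon signed-rank test of the difference, Spearman correlation, Bland-Altman plots and agreement in tertiles. The EE–EI difference is also the end point of the sample size calculation.

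For the urinary markers, the article explains its choice by saying that "errors are likely to be independent between the measurements of biomarkers and dietary intake". It makes no such statement for energy. The Limitations mention that doubly labeled water was not used, but not that TEE may contain part of EI.

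**The concern.** If DIT is 10% of the energy reported in the recall, the method under test forms part of its own reference. A participant who under-reports intake is also assigned a lower expenditure, so part of the error cancels in the difference and appears as agreement in the ranking. This always favours the tool. It differs in kind from the limitation already stated: a reference that is merely less accurate than doubly labeled water does not by itself lean toward the method being validated. GloboDiet is intended for national nutrition monitoring, so an avoidable lean in its favour for energy matters.

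**Working it through.** **The plan's own figure.** The sample size section gives power above 0.998 for a two-sided paired t test at α = 0.05 with 50 women and 50 men. It defines d but gives no value, so the power cannot be recomputed forward. Solved backwards with the noncentral t, 0.998 needs d ≈ 0.70 at n = 50, or d ≈ 0.49 at n = 100. This is possible but not verifiable. Step 2 shows that d is the same under either reference.

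**Step 1: the difference.** Let R = RMR + AEE, neither of which uses the recall.

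- As written: TEE = R + 0.1·EI.
- Recall-free, with DIT as 10% of expenditure: TEE* = R/0.9.
- EI − TEE = 0.9·EI − R = 0.9 × (EI − R/0.9) = 0.9 × (EI − TEE*).

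Relative to TEE*, the mean bias and both limits of agreement are multiplied by 0.9. Example with an assumed TEE* of 2400 kcal and 20% under-reporting: EI = 1920 and R = 2160, so TEE = 2160 + 192 = 2352. The bias reads 1920 − 2352 = −432 instead of 1920 − 2400 = −480 kcal.

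**Step 2: the test against zero.** Multiplying every difference by 0.9 leaves d, the t statistic, the signed ranks and the p values unchanged. A simulated sample of 82, the number with activity data, gave identical t and Wilcoxon p values under both references.

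**Step 3: correlation and tertiles.** The article gives no SDs, so these are assumptions: SD(EI) 450–800 kcal, SD(R) 400–450 kcal, bivariate normal. With ρ the Pearson correlation of EI and R,

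corr(EI, R + 0.1·EI) = (ρ·SD(R) + 0.1·SD(EI)) / √(SD(R)² + 0.2·ρ·SD(R)·SD(EI) + 0.01·SD(EI)²).

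At ρ = 0 and SDs of 450 and 450: 45/√(202,500 + 2,025) = 0.10. At SD(EI) 800 and SD(R) 400: 80/√(160,000 + 6,400) = 0.20. On the Spearman scale:

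| Spearman, EI with R/0.9 | Spearman, EI with R + 0.1·EI |
|---|---|
| 0 | 0.10–0.19 |
| 0.19 | 0.28–0.36 |
| 0.29 | 0.37–0.45 |

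With no association, the share in the same tertile rises from 33% to 36–39%.

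**Step 4: how much of that rise is artefact.** Let T be true intake that day and EI = T + e, with e the recall error, assumed independent of T and R. On the article's definition, error-free expenditure is R + 0.1·T, so only 0.1·e is shared error. Let T explain a share k of the variance of EI. At ρ = 0 the error-free correlation (Pearson) is

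0.1·k·SD(EI) / √(SD(R)² + 0.01·k·SD(EI)²).

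For k from 0.5 to 0.9 over the same SDs this is 0.05–0.18, against 0.10–0.20 with reported EI. At k = 0.5 about half of the rise is artefact; at k = 0.9 about a tenth.

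**Step 5: the 10% seen the same way.** EI − TEE = [EI − (R + 0.1·T)] − 0.1·(EI − T). The mean bias is therefore pulled toward zero by 10% of the mean recall error. If the group is in energy balance, mean recall error equals the true mean bias and the 10% holds. For the width of the limits only the e component shrinks, so against R + 0.1·T the narrowing lies between 0 and 10%.

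**The case against.** The strongest objections, and what stands of each:

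- **The key step is inferred.** The DIT sentence is a cited physiological statement. Nothing says how DIT was computed per person, and a condensed article may omit it. This stands as a limit on certainty. But no other same-day intake source is described, and if DIT was in fact taken as a share of expenditure, the sentence is misworded and still needs correcting.
- **The recall-free reference has its own assumption.** R/0.9 equals R plus 10% of that day's intake only in energy balance. This stands: it is reasonable for a group mean and approximate for one person on one day.
- **Part of the correlation is physiology.** Someone who ate more does expend more. This stands (step 4), so a reader who takes the whole rise from 0 to 0.10–0.19 as false agreement goes too far.
- **The effect on bias is small.** In the example it is 48 kcal on 2400, or 2%. True, but its direction is fixed and it is easily removed.
- **Other checks do not contain the shared term.** EI is also compared with RMR, and protein and potassium with urine; the Goldberg and Black cutoffs are likewise free of it if based on EI:RMR. This stands and limits the reach of the problem.

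Two further inferences are tempting. One is that the sample-size end point is compromised: its test and power are unchanged (step 2). The other is that the article contradicts its own claim of independent errors: that claim is made for nitrogen and potassium only, where the shared term plays no part.

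**Conclusion.** The point holds at moderate severity. On the text as written, TEE appears to include about 0.1 × EI from the recall it is used to validate, and nothing elsewhere in the article corrects or discloses this. Mean bias and limits of agreement are 10% smaller than against R/0.9; that figure is algebra, but reading it as understatement of the true discrepancy rests on energy balance. Spearman and tertile agreement are raised by an amount that depends on SDs the article does not give, and under the assumptions shown between about a tenth and a half of that rise is artefact. A reader might conclude that the energy validation as a whole is unsound. The documents do not support that: the zero-difference test and its power, the EI–RMR comparison and the nitrogen and potassium validation are untouched.

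**What to change.** Compute TEE without reported intake, as (RMR + AEE)/0.9, and state that this assumes energy balance. Use it for the EI–TEE difference, the Bland-Altman plot, Spearman and tertiles. Correct the DIT sentence in the Methods so that it says what DIT is a share of and where the figure comes from. If the formula as now written is also reported, present it as a sensitivity analysis and name the shared term in the Limitations beside the remark on doubly labeled water. The cost is one changed formula, a re-run of the EI–TEE analyses and a few sentences of text. No new data are needed, and the reported agreement for energy will probably look slightly less favourable.
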